## Abstract

**Background:**

Sex workers (SWs) are at risk of acquiring HIV infections. Despite this, SWs have low uptake of relevant preventive measures, such as HIV pre-exposure prophylaxis (PrEP). Community-based programs that make PrEP convenient and accessible have the potential to drive PrEP continuation and reduce HIV risk.

**Objective:**

This study aims to describe the co-development and piloting of the Together Optimizing PrEP Access in Zimbabwe (TOPAZ) intervention—where SWs have the opportunity to access PrEP refills through pharmacies in Zimbabwe.

**Methods:**

Using a participatory process, the TOPAZ intervention will be collaboratively developed with pharmacy owners and SWs. TOPAZ comprises the provision of safe and convenient spaces for PrEP refill pickups bundled with a gift voucher incentive at pharmacies. Formative research comprising focus group discussions and in-depth interviews with SWs, pharmacists, and stakeholders will inform the development of the preliminary model (aim 1). A cluster-randomized pilot trial will evaluate the impact of the PrEP-in-pharmacy intervention, compared to standard clinic-based pickup in the key populations program, on PrEP retention at 3, 6, 9, and 12 months after initiation (aim 2). The outcome of the pilot trial will be a comparison of PrEP retention at 6 months after initiation between study arms. We will also compare PrEP retention among SWs aged between 18 and 24 years at 6 months and among participants remaining active in sex work at 6 months. We will use the Generalized Estimation Equations model to generate risk differences and 95% CIs for PrEP retention in intervention versus comparison arms. Analysis will follow an intent-to-treat approach. Finally, a mixed methods study will be conducted to understand the potential for scaling TOPAZ for SWs; insights from this study will inform the design of a future effectiveness trial (aim 3). Proctor’s implementation outcomes, namely, acceptability, adoption, appropriateness, feasibility, fidelity, and penetration of the pharmacy-based PrEP refill program, will be evaluated by triangulation of program data and qualitative interviews.

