#### Procedures for the Standard-of-Care Arm

SWs enrolled as part of the TOPAZ study in the standard-of-care arm will initiate PrEP following the KP program standard operating procedures. They will be recruited through the KP program outreach clinics; undergo HIV testing; and if they are HIV negative, they provide verbal consent for PrEP initiation and collection of subsequent refills. At each visit, SWs will receive PrEP plus counseling on the importance of adhering to the prescribed PrEP schedule. PrEP refills will be recorded on standardized paper-based data collection tools, per the KP program standards, and will be analyzed from the program records.

Inclusion criteria for enrollment into the TOPAZ standard-of-care arm are (1) initiated on PrEP through the KP program’s mobile outreach clinics operating in 1 of the 4 standard-of-care suburbs, (2) aged >16 years, (3) having exchanged sex for money in the last 6 months, and (4) providing verbal consent.

All participants will receive a US $5 transport reimbursement at the end of each visit. Participants in the standard-of-care arm will be advised that they can collect PrEP refills from the KP program clinics, following standard procedures. Participation in the intervention will continue for 12 months.

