#### Recruitment of FSWs in PrEP-in-Pharmacy Intervention Suburbs

FSWs initiating PrEP will be informed that enrolling as an intervention participant is voluntary and their refusal will not interfere with the KP program standard of care, including their ability to access PrEP. FSWs will also be given information about the intervention and the associated risks in detail. Interested FSWs will be given an information flyer, and consent to participate will be obtained verbally. Information flyers will be available in the 3 main languages spoken in Zimbabwe: English, Shona, and Ndebele. The eligibility criteria to participate in the intervention arm are (1) initiated on PrEP through the KP program’s mobile outreach clinics in 1 of the 4 intervention suburbs, (2) aged >16 years, (3) having exchanged sex for money in the last 6 months, and (4) providing verbal consent to enroll in the TOPAZ study.

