#### Outcomes

##### Outcome 1: Retention on PrEP at 6 Months

This will be measured as attendance within a window of −7 to +7 days of the scheduled 6-month refill visit. Outcome 1 will be expressed as the proportion of 6-month visits completed as scheduled, overall and by arm.

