##### Outcome 3: Patronage for PrEP Services at Pharmacies

FSWs (overall) and FSWs (aged between 18 and 24 years) patronage for PrEP services at pharmacies, defined as the proportion of all PrEP refill pickups (1, 3, 6, and 12) in intervention suburbs occurring at pharmacies, overall and by pickup month.

#### Data Analysis for Aim 2

For retention outcomes at 1, 3, 6, 9, and 12 months, the KP program database will be used to compare the number and proportion of FSWs retained on PrEP as defined earlier by study arm. We will conduct an intent-to-treat analysis to estimate the intervention’s effect using a cluster-based permutation test applied to the individual-level binary outcome (retained on PrEP and not retained on PrEP) using the *cptest* function in the R cvcrand package (or a similar function). The permutation test will be conducted with the same covariates used during the constrained randomization process at the suburb level (expanded from the values of the cluster-level covariates, according to which cluster everyone belongs). This approach will be repeated for the other outcomes. To produce a measure of effect, a Generalized Estimation Equations model will also be constructed to generate a risk difference of PrEP retention among people initiating PrEP in intervention versus comparison suburbs and a 95% CI. In accordance with the CONSORT (Consolidated Standards of Reporting Trials) guidelines, unadjusted estimates will be reported, and the preregistered analysis plan at ClinicalTrials.gov will specify an adjusted model in the case of baseline imbalances. Overall, this analysis framework permits causal attribution.

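### The abstract's arm comparison among women still in sex work at month 6 rests on a post-randomisation subgroup, so it is not intent-to-treat, and the outcome list omits it

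*Protocol article*

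**What the plan says.** The Methods paragraph of the abstract names the 6-month comparison between arms, then adds two more: one in younger women, and one "and among participants remaining active in sex work at 6 months". It goes on to say that a GEE model will give risk differences, and closes the topic with "Analysis will follow an intent-to-treat approach".

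In the body, Outcome 1 defines retention: "This will be measured as attendance within a window of −7 to +7 days of the scheduled 6-month refill visit". It continues: "Outcome 1 will be expressed as the proportion of 6-month visits completed as scheduled". Outcome 2 is the same measure at ages 18 to 24, and Outcome 3 is use of pharmacies for refills. No outcome concerns women still selling sex at month 6.

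Selling sex enters the trial only as an eligibility criterion, looking back from enrolment: "3) having exchanged sex for money in the last 6 months". The standard-of-care arm has the same criterion.

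On data sources:
- Standard-of-care arm: "PrEP refills will be recorded on standardized paper-based data collection tools, per the KP program standards, and will be analyzed from the program records".
- Intervention arm: a REDCap tool on tablets, organised around scheduling and dispensing refills.
- Data Analysis for Aim 2: "the KP program database will be used to compare the number and proportion of FSWs retained on PrEP". That section ends by saying that the framework supports causal conclusions.

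The overview of KP program services adds that women who miss a refill are followed up by telephone, messages and peers.

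**The concern.** Randomisation makes the two arms comparable as enrolled. A subgroup that forms six months later is not protected by it: the intervention may influence who belongs, and membership may be related to staying on PrEP. A comparison inside such a subgroup is not intent-to-treat, and the causal claim in the analysis section cannot be carried over to it. This holds even if every woman's status were known.

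A second problem comes on top. Membership and outcome refer to the same time point, and the outcome is a visit. If status is learned mostly at visits, women who are not retained drop out of the denominator more often than women who are. Subgroup retention is then too high in both arms, and the difference between arms can move in either direction.

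At stake is a secondary result that could be read as an effect among women still at risk and carried into the design of the later effectiveness trial.

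**Working it through.** **1. Does the body support the comparison?** Set side by side, the abstract lists overall retention, retention in younger women and retention in women still selling sex. The outcome section lists overall retention, retention at ages 18 to 24 and pharmacy patronage. The third abstract comparison has no counterpart in the body.

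**2. Is it intent-to-treat?** Membership is fixed at month 6, after randomisation, and the outcome is attendance within 7 days either side of the month-6 visit. Conditioning on such a variable departs from comparing everyone as enrolled. No data assumption is needed for this step.

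**3. How much could incomplete status matter?** The article gives no figure for this subgroup, so there is none to reproduce. The following is an illustration.

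Inputs:
- True retention R: 14% in control and 50% in intervention, from Sample Size and Power Calculations. True difference: 36 points.
- a: share still selling sex at month 6, assumed independent of arm and of retention.
- Status known for every retained woman (assumption).
- q: share of women not retained whose status is learned. The article gives no value, so a range is shown.

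Formula: observed subgroup retention = aR / (aR + a(1 − R)q) = R / (R + (1 − R)q). The share a cancels.

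Equal q in both arms:

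| q | Control | Intervention | Difference |
|---|---|---|---|
| 0 (limit) | 100% | 100% | 0 |
| 0.10 | 0.14/0.226 = 62% | 0.50/0.55 = 91% | 29 points |
| 0.20 | 0.14/0.312 = 45% | 0.50/0.60 = 83% | 38 points |
| 0.50 | 0.14/0.570 = 25% | 0.50/0.75 = 67% | 42 points |
| 1 | 14% | 50% | 36 points |

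Unequal q with no true effect (R = 14% in both arms):
- q = 0.50 in control, 0.25 in intervention: 0.14/0.570 = 24.6% vs 0.14/0.355 = 39.4%, a spurious difference of about +15 points.
- Shares reversed: about −15 points.

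Unequal q is plausible, because the arms use different recording tools (paper forms and REDCap), but the article gives no evidence that it occurs.

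**The case against.** The strongest objection is that the ascertainment problem is inferred from silence. The article does not say how month-6 sex-work status is obtained, for anyone. It condenses a fuller protocol, and such detail is commonly left there. Women who miss refills are contacted routinely, which could reveal their status. The Discussion also mentions self-reported adherence, which the data-collection sections do not describe, so the listed sources are evidently not complete.

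This objection stands against two stronger readings that a reader might infer. The first is that women who do not attend have no recorded status. The documents do not say so; they support only that status is probably known less often for women not retained. The second is that the comparison must collapse to 100% vs 100%. That is a limiting case. Retention requires attendance inside the window, so a woman who comes on day 8 or returns at month 9 counts as not retained and yet is seen.

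It is also fair to say that equal partial tracing at 20% or 50% moves the risk difference by only about 2 to 6 points, although the levels in each arm shift far more. The larger distortion needs either very little tracing or tracing that differs by arm.

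Finally, the analysis section refers to a preregistered plan that is not at hand, and data collection has ended. Deleting a publicly stated comparison now could look like selective reporting. That bears on the remedy.

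None of this touches the timing of the subgroup or the mismatch between the abstract and the outcome list.

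**Conclusion.** The point holds in two parts of different strength.

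Firm, and independent of any assumption about data: the comparison conditions on a post-randomisation state that coincides with the outcome, it is not intent-to-treat, the causal claim does not extend to it, and the body's outcome list omits it.

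Probable, with unknown size: status is known less often for women not retained, which inflates retention in both arms. Under the stated assumptions, equal tracing of 20% to 50% gives differences of about 38 to 42 points against a true 36, and 10% tracing gives 29. Tracing of 50% against 25% can produce about 15 points in either direction from a true null. These figures rest on independence of activity from arm and retention; if that fails, the values of 14% and 50% are themselves no longer the truth within the subgroup.

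A reader might infer that the main result is compromised. It is not: the primary comparison of overall retention does not use this subgroup. The progression criteria are assessed qualitatively and do not name it.

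**What to change.** Do not present this comparison as an intent-to-treat effect. Keep all enrolled women in every retention denominator, and report leaving sex work descriptively, as a reason for non-retention, by arm.

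If the comparison is kept because it was publicly stated, label it exploratory and non-randomised, report by arm how many women have unknown month-6 status, and state how status was obtained. In either case, reconcile the abstract with the outcome list.

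The cost is wording and a little tabulation. One secondary comparison loses its causal interpretation. Since data collection has ended, this can be settled before the analysis planned for February 2026 without any change to conduct.

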**Results:**

This study began the enrollment of participants in March 2024. Data collection ended in May 2025. The final comprehensive analysis of the results will be conducted in February 2026 after all the data have been collected and reviewed comprehensively.

**Conclusions:**

This study will report on the feasibility, acceptability, and effectiveness of pharmacy-based PrEP refills to improve PrEP continuation among women who sell sex. If successful, this preliminary study will pave the way for a future effectiveness trial to evaluate this intervention more comprehensively.

**Trial Registration:**

ClinicalTrials.gov NCT06348069; https://clinicaltrials.gov/study/NCT06348069

**International Registered Report Identifier (IRRID):**

DERR1-10.2196/74141

## Introduction

### Background

Sex workers (SWs) are disproportionately affected by HIV and contribute a 4-fold higher HIV prevalence than adults in the general population [1]. The relative risk of acquiring HIV among SWs globally is 9 times higher than the general population, while in sub-Saharan Africa, the relative risk of HIV acquisition is 11 times higher in SWs than the general population [2]. Data from generalized HIV epidemics in sub-Saharan Africa reveal that SWs and their clients account for >30% of HIV infections and 17% of incident HIV infections [2,3]. In Zimbabwe, HIV prevalence among female SWs (FSWs) is >50%, and the annual estimated incidence is 4%, translating to a 10-fold higher incidence than women in the general population [4,5]. New entrants into sex work and young women who sell sex are at the highest risk of HIV infection [5-8]. For example, HIV prevalence increases sharply from 2% for an FSW aged 16 years to >50% for an FSW aged 24 years in Zimbabwe [4,6-9]. These alarming statistics underscore a need to strengthen the effective use of HIV prevention for FSW, particularly among younger FSW, both to protect them from HIV and to support broader HIV epidemic control efforts [10-12].

Oral pre-exposure prophylaxis (PrEP) has demonstrated high efficacy in clinical trials, preventing >92% of new HIV infections when taken as prescribed [13]. However, implementation in real-world contexts has been disappointing, with low uptake and suboptimal continuation. Thus, strengthening motivation, capability, and effective use of PrEP among SWs, including younger FSWs, has the potential to reduce the rate of new infections among both SWs and the general population more broadly [5]. Mathematical modeling data from South Africa anticipate that high uptake and continuity of PrEP could theoretically lead to a population-level reduction in HIV incidence by 40% [7,8].

Although PrEP uptake reduces HIV risk, effective PrEP use and continuation is very low among populations considered high risk, such as SWs [14-16]. Studies from Benin (45%), Rwanda (22%), and Senegal (27%) reported lower PrEP discontinuation within 12 months when compared to South Africa (91%) and Zimbabwe (86%) [16-21]. These differences underscore the need to identify barriers to PrEP continuation toward developing context-specific interventions.

A host of factors impede PrEP uptake and continuation among FSWs, but of relevance to this intervention are fear of stigma associated with PrEP and lack of convenient access [20,22]. The World Health Organization recommends differentiated service delivery to diversify PrEP delivery, overcome barriers to access, and strengthen PrEP continuation [23]. Developing interventions outside the “brick-and-mortar” health clinics, for example, private pharmacies, may decentralize PrEP services and improve access [24-28]. Pharmacies are proven community-based channels that advance self-care initiatives in sexual and reproductive health and may be tailored to deliver PrEP for individuals considered high risk. Developing pharmacy-based PrEP service delivery models for SWs could make PrEP more accessible and improve PrEP uptake and continuation.

Successful delivery of pharmacy-based PrEP is contingent on collaborative efforts between policy makers, communities, and pharmacists [14,15,29-35]. This study aims to explore whether providing SWs with the option of PrEP refill supported by HIV testing through community-based pharmacies is feasible, acceptable, and increases effective use of PrEP in Zimbabwe. Given that research shows that small, short-term incentives can also be used to increase habit formation and motivation to continue PrEP [36-38], our trial also includes provision of small incentives to motivate PrEP continuation. Our Together Optimizing PrEP Access in Zimbabwe (TOPAZ) study develops and tests this pharmacy-based PrEP intervention for FSWs in Zimbabwe.

### Study Aims

The overall goal of the TOPAZ study is to increase PrEP continuation among FSWs through a co-developed pharmacy-based intervention. Specific aims are as follows: aim 1 is to refine and operationalize pharmacy-based PrEP distribution, including an escalating incentive with FSWs and pharmacy owners to motivate PrEP continuation in FSWs; aim 2 is to determine whether the addition of pharmacy-based PrEP distribution increases PrEP retention among FSWs at 6 months compared to standard services; and aim 3 is to understand the PrEP-in-pharmacy program’s potential to scale and translate lessons learned into a future effectiveness study.

## Methods

### Overview

A mixed methods approach will be used to develop and pilot the PrEP-in-pharmacy refill intervention for SWs, as summarized in Figure 1. The PrEP-in-pharmacy refill intervention will be available to all SWs in their diversity, including male and transgender workers; however, this study will formally assess outcomes among FSWs. To achieve aim 1, formative research to co-develop the intervention with SWs and pharmacists will be conducted. To achieve aim 2, the intervention will be piloted through an existing key populations (KP) program. A 1:1 cluster-randomized control design will be used to allocate 8 suburbs to 4 intervention or 4 standard-of-care suburbs. To achieve aim 3, a process evaluation will be conducted using a mixed methods implementation science framework to determine the feasibility, acceptability, and scalability of the intervention and to optimize future versions of the program.

**Figure 1 figure1:**
[figure not shown]
Overview of the Together Optimizing PrEP Access in Zimbabwe (TOPAZ) study design. KP: key populations; MoHCC: Ministry of Health and Child Care; PrEP: pre-exposure prophylaxis; SW: sex worker.

### Theoretical Model Informing the Implementation

This research draws on 2 primary theoretical models of behavior change: the Capability Opportunity Motivation model of behaviour change and behavioural economics Capability Opportunity Motivation Behavior (COM-B) model of behavior change and behavioral economics (Figure 2 [39]) [37,38]. The pharmacy intervention will be designed to increase *motivation* through knowledgeable and friendly pharmacists plus the peer outreach and support services already provided by the existing KP program. In addition, small incentive gift vouchers that can be redeemed for pharmacy products offered to FSWs for collecting PrEP refills at pharmacies will also increase *motivation*. *Access* will be increased through PrEP provision at pharmacies, and *effective use* will be increased by combining pharmacy-based access with short-term, escalating incentives (gift vouchers) to encourage continued PrEP refills [38]. Underpinning the incentive component of the intervention is behavioral economic theory, which posits that using simple, scalable “nudges” (norms, commitments, and incentives) that capitalize on common biases can influence behavior [40]. This approach is particularly useful when applied to behaviors that are new (such as taking PrEP) or those that can be viewed as unimportant or inconvenient (such as collecting PrEP refills, especially due to present-biased preferences) [41]. Escalating incentives leverage the behavioral economics concept of *loss aversion*, increasing “losses” are faced each time a refill visit is missed, a simple yet powerful motivator to stay engaged with PrEP [42-44].

**Figure 2 figure2:**
[figure not shown]
Application of the Capability Opportunity Motivation Behavior model in the current PrEP delivery for YWSS and FSWs in Zimbabwe and the contributions of the proposed intervention, which provides friendly, pharmacy-based PrEP distribution by informed pharmacists plus financial incentives (adapted from the study by Schaefer et al). FSW: female sex worker; PrEP: pre-exposure prophylaxis; SES: socioeconomic status; YWSS: young women who sell sex.

### Ethical Considerations

The TOPAZ study has obtained ethics approval from the national ethics review committee in Zimbabwe, the Medical Research Council of Zimbabwe (MRCZ/A/2988), and the University of California Berkeley Committee for Protection of Human Subjects (2022-11-15783). All study procedures will be conducted in accordance with the Declaration of Helsinki. All participants will be informed about the study and will provide consent to participate, as outlined in the following sections describing the various study activities. Participant data will be deidentified and stored in secure databases, with identifiable data, such as full names (only in the informed consent), stored separately. Adverse occurrences throughout the study will be recorded in a log that will be shared with the national ethics review board.

